## Abstract

**Introduction:**

The Mobile Health (mHealth) Intervention for Dementia Prevention through lifestyle Optimisation (MIND-PRO) study addresses the increasing prevalence of dementia among populations with lower socio-economic status (SES) and/or a migration background. The study aims to evaluate the effectiveness and implementation of an mHealth intervention designed for self-managing lifestyle modifications with remote coaching to reduce dementia risk factors.

**Methods and analysis:**

This prospective randomised open-label blinded end point (PROBE) trial follows a type 2 hybrid effectiveness-implementation design with a 12-month intervention period. It aims to recruit 692 participants in Dutch primary care. Entry criteria include age 50–75 years, low SES and/or migration background, one or more dementia risk factors (hypertension, dyslipidaemia, diabetes mellitus, physical inactivity, smoking, depression and overweight) or manifest cardiovascular disease and possession of a smartphone. Participants are randomised to a coach-supported, interactive app facilitating self-management of dementia risk factors or to a control app with static health information. The primary effectiveness outcome is a composite score of systolic blood pressure, non-high-density lipoprotein cholesterol and body mass index. Implementation outcomes include coverage, adoption, acceptability, appropriateness, feasibility, fidelity, costs and sustainability of the intervention. Secondary outcomes include the Cardiovascular Risk Factors, Ageing and Dementia risk score and its individual risk factors, and disability, physical activity, depressive symptoms, cognitive functioning and daily distance moved.

**Ethics and dissemination:**

The MIND-PRO trial is funded by the Netherlands Organisation for Health Research and Development (ZonMw, grant number 10510032120004) and approved by the Ethics Committee of Amsterdam UMC (reference: METC 2023.0770). Results are expected in 2026 and will be submitted for publication in a peer-reviewed journal, and presented at scientific conferences.

**Trial registration number:**

ISRCTN92928122.

STRENGTHS AND LIMITATIONS OF THIS STUDYParticipants were selected to represent a high-risk, diverse group, including individuals with lower socio-economic status and migration backgrounds.This group is under-represented in conventional preventive initiatives, highlighting the importance of tailored, culture-sensitive interventions.In this proof-of-concept trial, both effectiveness and implementation of the intervention will be evaluated using a hybrid trial design.A potential limitation, common in preventive studies, is the risk of selection bias as participants might be healthier and more motivated to change their lifestyle.

## Introduction

### Background and rationale

 The global prevalence of dementia is expected to rise in the coming decades, which can primarily be attributed to population ageing and growth.^1^ Up to 40% of dementia is associated with modifiable risk factors, including high blood pressure, physical inactivity, unhealthy diet, overweight and smoking.^2^ These risk factors largely overlap with those of cardiovascular disease (CVD).^3^ Even a modest reduction of 10% in these risk factors can potentially have a major long-term impact on the prevalence of dementia due to the frequent occurrence of these risk factors, underlining the importance of preventive measures.^2^

The increase in dementia prevalence is not equally distributed worldwide. People living in low- and middle-income countries and people of lower socio-economic status (SES) and/or migration background, in high-income countries carry the highest burden.^1 4^ This could be attributed to the clustering convergence of risk factors within these groups,^5^ and restricted access to healthcare and prevention programmes.^6 7^ Within these high-risk groups, there is greater potential for improvement, yet they are frequently under-represented in prevention trials. The widespread use of mobile phones, coupled with increasing access to the internet via mobile devices, provides an opportunity for using Mobile Health (mHealth) technology to reach these underserved populations.^8^ It is crucial for developers of mHealth interventions and healthcare policymakers to recognise that these innovations have been primarily adopted by younger, highly educated individuals. This phenomenon inadvertently excludes people with lower (health) literacy skills, exacerbating the existing health inequality gap.^9 10^ In this study, we aim to mitigate this challenge by involving our target population in the process of developing the mHealth Intervention for Dementia Prevention through lifestyle Optimisation (MIND-PRO) intervention to ensure it is culture-sensitive and appropriate for those with low SES and/or a migration background.^11^ We will build on the lessons learnt from the Prevention of Dementia by Mobile Phone Applications (PRODEMOS)^12^,^14^ and the Healthy Aging through Internet Counseling of the Elderly (HATICE)^15^,^17^ trials to further improve a coach-supported smartphone app and tailor it to a population with a migration background and/or low SES facing elevated dementia risk in the Netherlands. The MIND-PRO trial aims to investigate the effectiveness and implementation of this culture-sensitive app supporting lifestyle modification to lower dementia risk factors through self-management and remote coaching during 12 months intervention.

## Methods

### Study design

The study is a single-centre, investigator-initiated, prospective, randomised, open-label blinded end point (PROBE) trial with 12 months intervention, conducted in the Netherlands. A type 2 hybrid implementation-effectiveness design will be used to assess proof of concept for effectiveness and implementation.^18^ The MIND-PRO trial is a project within the Netherlands Dementia Prevention Initiative (NDPI), part of the Dutch National Dementia Plan.

### Study population and recruitment

People aged between 50 and 75 years with a basic level of literacy in Dutch, of low SES and/or Turkish or South-Asian Surinamese origin, with one or more dementia risk factors or manifest CVD and in possession of a smartphone, are eligible for participation. Participants will be primarily recruited from the Healthy Life in an Urban Setting (HELIUS) study, a population-based observational prospective cohort within the largest migrant populations of Amsterdam, including the Dutch host population (n=24 781 included at baseline).^19^ By building on the HELIUS study infrastructure, we will be able to select and invite potential participants based on SES, ethnic origin and dementia risk factors, as these variables are available in the HELIUS database.^19^ Additional recruitment will be conducted through primary care practices if the target sample size cannot be achieved with HELIUS participants alone. Eligibility criteria for the RCT are summarised in box 1. Low SES is operationalised using self-reported educational attainment in the Netherlands or in the country of origin, specifically defined as (i) ‘none or only primary education’, (ii) ‘lower vocational or lower secondary education’, (iii) ‘intermediate vocational or intermediate or higher secondary education’ as previously collected in HELIUS.^19^ All participants will provide written informed consent (online supplemental appendix 2).

Box 1Overview of eligibility criteriaExclusion criteriaDiagnosed with dementia by a specialist or general practitionerA score <21 on the Rowland Universal Dementia Assessment Scale^24^Any condition expected to limit 12 months compliance and follow-upAny impairment interfering with operation of a smartphoneParticipating in another randomised controlled trial on lifestyle behavioural changePresent alcohol or illicit drug abuse impairing study participation

### Intervention and control condition

Participants randomised to the intervention arm will get access to an mHealth app aimed at lifestyle behavioural change, supported by a coach. This interactive app facilitates self-management of dementia risk factors (hypertension, dyslipidaemia, active smoking, overweight, lack of physical exercise and unhealthy diet). The participants will be supported by an experienced lifestyle coach trained in motivational interviewing, who will be matched to the ethnicity of the participants with one of the coaches able to speak Turkish for Turkish participants. The coaches will assist participants in formulating simple, measurable, achievable, realistic and time-bound (SMART) goals and support them in achieving these goals. Their role is to guide them in their lifestyle change. They are instructed to recommend participants with medical questions to seek help from their doctor. Also, mental health-related questions are beyond the scope of our intervention, and will result in a recommendation to visit their doctor. Participants can contact the coach via the app through chat, and coaches will be motivated to stay in contact with the participants at least once a month. After secure login, the app shows the participants’ dementia risk profile, based on baseline assessment. Participants can set goals for lifestyle change, monitor these goals and enter self-measurements, for example, weight, blood pressure and physical exercise. Progress over time is visually presented whenever feasible. Additionally, the app contains evidence-based education modules, including educational videos specifically designed for this study population, featuring the health coaches. The intervention app will be available in three versions for each ethnicity, with culturally acceptable content. The two versions for the Dutch and South-Asian Surinamese population will be available in Dutch; the version for the Turkish population will be available in both Dutch and Turkish. Those randomised to the control condition will have access to an app which is similar in appearance, but lacks the interactive features of coach-support and monitoring risk factors. Participants are informed that there are two versions of the app and that they will be randomly assigned to one. They are not made aware that one app serves as the active intervention while the other represents the control condition. The control app provides only static information about healthy lifestyles, without incorporating culturally specific content, and is available in both Dutch and Turkish.

### Patient and public involvement

During the development process of the app, our target population and mHealth software engineers were actively involved, as shown in figure 1. The initial concept of the MIND-PRO app was based on insights from prior eHealth and mHealth trials conducted by our research team, specifically the from HATICE^16^ and PRODEMOS^20^ studies. The app was subsequently refined through iterative feedback cycles, resulting in an optimised version tailored to the needs and wishes of the target population for use in this trial. To achieve this, we conducted semi-structured interviews and focus groups to gain a deeper understanding of participants’ perspectives and their requirements for a coach-supported lifestyle intervention.

**Figure 1 F1:**
[figure not shown]
Design process of the intervention. In this figure, the process of co-creating the intervention is illustrated. The researchers, mHealth software engineers and end-users worked in iterative cycles of feedback to co-create the app. Semi-structured interviews, focus groups and a pilot phase were conducted to identify barriers and facilitators, which led to adaptations to the app. mHealth, Mobile Health; MIND-PRO, mHealth Intervention for Dementia Prevention through lifestyle Optimisation.

### Primary and secondary outcomes

Following a type 2 hybrid effectiveness-implementation design, equal weight will be placed on the effectiveness and implementation outcomes. The primary effectiveness outcome will be the difference between baseline and 12 months follow-up of a composite z-score of systolic blood pressure, non-high-density lipoprotein (HDL) cholesterol and body mass index (BMI). The secondary effectiveness outcomes include changes from baseline in CAIDE dementia risk score,^21^ individual modifiable components of the CAIDE risk score, questionnaires on physical activity,^22^ disability,^23^ depressive symptoms^24^ and cognitive functioning,^25 26^ cost-effectiveness analysis including intervention costs and daily distance moved measured by Behapp. Depressive symptoms are an outcome, because indirect effects may occur, for example, through increased physical activity. Cognitive functioning will be tested with The Rowland Universal Dementia Assessment Scale (RUDAS) and the Box Task for a computerised assessment of visuospatial working memory.^27^ Two parallel forms of the RUDAS were created for repeated administration at the beginning and end of the trial. Daily distance moved will be measured using a separate smartphone application (Behapp), which is optional and for which separate informed consent will be asked. Behapp has been developed and is operated by The University of Groningen to provide a remote, unobtrusive and objective measure of overall social mobility in a longitudinal daily-life manner. An in-depth explanation of Behapp, as well as the privacy and security measures, deployed by Behapp are described in detail previously.^28^ Effectiveness outcomes are summarised in table 1.

**Table 1 T1:** Effectiveness outcomes

Primary outcomes
Composite score of systolic blood pressure, non-HDL cholesterol and body mass index (BMI)

Secondary outcomes	Measurement tool
(1) Physical exercise	Self-administered short International Physical Activity Questionnaire-Short Form^22^
(2) Disability	WHO Disability Assessment Schedule 2.0 (12-item)^23^
(3) Depressive symptoms	Geriatric Depression Scale 15-item^24^
(4) CAIDE dementia risk score	Cardiovascular Risk Factors, Ageing and Dementia^21^
(5) Individual modifiable components of the CAIDE risk score	Age (≥47 years), education (<10 years), sex, systolic blood pressure, obesity (BMI ≥30), physical activity and total cholesterol
(6) Intervention costs	Costs of coaches and app intervention development
(7) Cost-effectiveness	Cost-effectiveness analyses are clarified in online supplemental appendix 1
(8) Cognitive functioning	The Rowland Universal Dementia Assessment Scale^26^ and the Box Task^27^
(9) Daily distance moved	Behapp, a remote behavioural monitoring app^28^

The implementation of the intervention will be measured using implementation outcomes reflecting coverage, acceptability, adoption, appropriateness, feasibility, fidelity, costs and sustainability.^29^ All implementation outcomes and evaluation methods are shown in table 2.

**Table 2 T2:** Summary of implementation research methods and outcomes

Method	Implementation outcome^7^	Measurements	Population	When measured
Quantitative	Coverage	(Non)response rates, comparison characteristics participants with eligible/source population	Potential target population	At baseline
	Adoption	Quantitative analysis of the utilisation, usage and uptake—for example, logins, goals setting, sending messages	All intervention participants	After 1 month (data features)
	Appropriateness	Short questionnaire of perceived fit or relevance*	All intervention participants	After 6 months and at study end
	Acceptability	Short questionnaire of agreeability, user-friendliness, credibility, complexity, content*	All Intervention participants	After 6 months and at study end
	Feasibility	The extent to which the mHealth intervention can be carried out	All intervention participants	After 6 months and at study end
	Sustainability	Adherence, dropout, data features (time spent in the app)	All intervention participants, dropouts	Data features throughout the study
	Implementation cost	Implementation costs (see cost-effectiveness analysis plan in online supplemental appendix 1)	n.a.	After 6 months and at end of study
Qualitative	Appropriateness	Perceived fit or relevance of the intervention	Intervention participants†; coaches	After 6 months
	Adoption	Initial utilisation, usage and uptake	Intervention participants†	After 6 months
	Acceptability	Agreeability, user-friendliness, credibility, complexity, content	Intervention participants†; coaches	After 6 months
	Feasibility	Practical and social barriers/facilitators related to the feasibility of the intervention	Intervention participants†; coaches	After 6 months
	Fidelity	Degree to which the mHealth application is implemented compared with the original protocol	Coaches	After 6 months
	Sustainability	Adherence	Coaches	After 6 months

* We used several questions from the validated mHealth App Usability Questionnaire for Interactive mHealth Aapps (MAUQ) (), where applicable to our intervention.^38^

† 30 participants (10 Dutch, 10 Turkish, 10 South-Asian Surinamese) will be invited for an interview on the implementation outcomes.

mHealthMobile Healthn.a.not available

### Study procedures

The study procedures are visualised in figure 2. Potentially eligible participants, based on information from the HELIUS study, will be invited via a letter in Dutch and Turkish to participate in the MIND-PRO study starting from July 2024 and ending in July 2026. The planned recruitment period is 12 months. We expect to be finished with recruitment in July 2025. A second invitation mail or email will be sent to those who did not respond to the first invitation. When there is still no response, we will call the potentially eligible participants to ask whether they want to participate. Those who are willing to participate will undergo a prescreening call to assess their eligibility for a further screening visit and subsequent baseline visit. During the screening visit, written informed consent will be obtained and additional measurements (weight, blood pressure, non-HDL cholesterol and assessment of cognitive functioning) will be conducted. Also, data on medication (antihypertensives, cholesterol-lowering drugs, diabetes treatments and antidepressants) will be collected. At the end of the screening visit, the MIND-PRO app will be downloaded with an explanation how to fill in the self-assessment questionnaires in the app. Participants will be asked to fill out the questionnaires themselves in the app. After the screening visit, the baseline visit will take place during which the self-assessment questionnaires will be checked and completed and the participant will be randomised to the intervention or control group, stratified by ethnicity. Six months after randomisation, participants will be requested to fill out a questionnaire on adverse events, which will be sent via the app. They will also be asked about their healthcare utilisation, specifically general practitioner visits, dietitian or physiotherapist visits and hospital visits. Additionally, all participants in the intervention group will be asked to fill out a questionnaire on implementation outcomes in the app 6 months after randomisation. Those who do not fill out the questionnaires will be called and the questionnaires will be administered by an assessor by telephone. For a more in-depth, qualitative assessment of implementation outcomes, a purposive sample from the intervention group of approximately 30 participants (10 from each ethnic group) will be asked to participate in an interview (table 2). At the end of the study, the questionnaires, medication use, healthcare utilisation and measurements performed during the screening visit will be repeated. Assessors will be matched to the participants’ ethnicity as much as possible.

**Figure 2 F2:**
[figure not shown]
Flow chart of study procedure. *An initial invitation will be sent to potentially eligible participants via mail. If there is no response, a second invitation will be sent via mail or email. If there is still no response, we will call the participants to ask if they are willing to participate.

### Randomisation and blinding

Randomisation will take place in the app using a computer algorithm in a 1:1 manner, stratified by ethnicity. Randomisation will be carried out by trained assessors at the baseline visit. Participants will be informed that they are randomised to one of two different smartphone apps that can provide support in changing their lifestyle to reduce the risk of dementia. Partners or first-degree family members who also participate in the MIND-PRO study will automatically be allocated to the same treatment arm to limit contamination. Outcome assessment will be performed by an assessor who is blinded to treatment allocation. The coaches who support participants in behaviour change are, due to the nature of the intervention, not blinded. A certain level of unblinding during outcome assessment is conceivable, since a participant could share details about participation in the MIND-PRO app specifically to the outcome assessor. Participants and assessors are therefore instructed to not discuss the intervention with each other. If any unblinding occurs, its impact is likely limited since our primary outcome consists solely of objectively measured parameters.

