## Statistical analysis and quality assurance

### Sample size

The sample size was calculated based on the expected effect of the intervention on our primary effectiveness outcome in individuals with low education, used as a proxy for low SES, from our previous prevention trials. In participants with a low educational level in the HATICE trial,^16^ the mean difference between intervention and control participants in change from baseline was 0.107 (pooled SD 0.454) for the composite z-score after 1.5 years. In the preDIVA trial,^30^ the difference in composite z-score between individuals with a low educational level who developed dementia and those who did not during 6–8 years of intervention was 0.096 after 24 months. Therefore, a mean difference in change of 0.107 was considered as potentially clinically relevant with respect to the risk of dementia. For the effect of the intervention within specific migrant groups, no data are available. With 277 participants per treatment arm, we will have 80% power (with alpha set at 0.05) to detect a 0.107 (pooled SD 0.454) difference on our primary effectiveness outcome. To adjust for an anticipated drop-out of 20% in this specific target population, 692 participants will be recruited.

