### Data analysis

The primary effectiveness outcome is the difference between the composite z-score after 12 months and the baseline composite z-score ((z_SBP_+z_non-HDL cholesterol_+z_BMI_)/3). The baseline mean and SD will be used to calculate composite z-scores at both time points to be able to detect a change. For the primary analyses, we will use a linear mixed effects model with individual observations nested within ethnic groups, operationalised by a random intercept and/or slope (depending on best model fit). If needed, we will explore the impact of any baseline imbalances by including imbalanced factors as a covariate in a sensitivity analysis. A per-protocol analysis will be done, based on uptake within the first month and continued use during the whole intervention period. Exploratory subgroup analyses on the primary outcome will be performed for ethnic group, sex, age group, history of CVD and diabetes.

We will conduct a sensitivity analysis using multiple imputation for the primary effectiveness outcome. Implementation of the intervention will be analysed with a series of implementation outcomes, as summarised in table 2. We will investigate frequency of app use and contact with the coach in relation to the effect on the primary outcome. We will graphically portray the Likert scales for the questionnaires and perform thematic analysis for the in-depth interviews. The interview guides can be found in the online supplemental appendix 3.

For the secondary outcomes, the effect on the CAIDE dementia risk score and its individual components (ie, blood pressure, BMI, total cholesterol, physical activity) will be analysed using the same model as for the primary analysis. In addition, as an exploratory analysis, the effect on daily changes in general movement will be assessed based on the data collected with the BeHapp application.^28 31 32^ For that purpose, time series analysis will be performed to detect trends in this longitudinal data as a function of intervention, accounting for clustering within ethnicities.

Scales for disability, depressive symptoms and cognitive functioning, mostly ordinal, will also be analysed as linear scales if the data characteristics allow. The same model as used for the primary analysis will be employed. Poisson regression or zero-inflated models may be applied to distributions resembling count or zero-inflated data. A description of the cost-effectiveness analysis can be found in online supplemental appendix 1.

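### Relatives are allocated to one arm together, but the primary model clusters only by ethnic group and the sample size has no design effect; if relatives' changes are positively correlated, the standard error is too small and power is overstated, probably by a modest amount

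*Protocol article*

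**What the plan says.** Three sections of the protocol article bear on this point.

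- **Randomisation and blinding.** The general rule is individual allocation: "Randomisation will take place in the app using a computer algorithm in a 1:1 manner, stratified by ethnicity". It has one exception: "Partners or first-degree family members who also participate in the MIND-PRO study will automatically be allocated to the same treatment arm to limit contamination".
- **Data analysis.** For the primary outcome, "we will use a linear mixed effects model with individual observations nested within ethnic groups", using a random intercept and/or slope chosen by model fit. The same model is carried over to the CAIDE score and its components, and to disability, depressive symptoms and cognition where they can be treated as linear scales. The movement data are likewise to allow for clustering by ethnicity. No family or household level appears in any of these.
- **Sample size.** With 277 per arm the trial is said to have 80% power at alpha 0.05 "to detect a 0.107 (pooled SD 0.454) difference on our primary effectiveness outcome". The only inflation is for attrition: "To adjust for an anticipated drop-out of 20% in this specific target population, 692 participants will be recruited".

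**The concern.** When a second family member enrols, that person's arm is already fixed by the first. The two are a small cluster allocated as a unit. If their outcomes are correlated, they carry less information about the treatment effect than two independently randomised people.

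The clustering term in the model does not deal with this. Both arms are present within each ethnic group, so ethnicity is a stratifier and not a unit of allocation. Relatives will usually share an ethnic group. Whatever makes them more alike than two unrelated members of that group stays in the residual, which the model treats as independent.

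The primary confidence interval and p-value are at stake, along with those of the outcomes that reuse the model. With positive within-family correlation the interval is too narrow and the test rejects too often under the null. A valid test has less power than the protocol states.

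**Working it through.** **Inputs from the Sample size section:** difference 0.107, pooled SD 0.454, alpha 0.05 (taken as two-sided), 277 per arm, 20% drop-out, 692 recruited.

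**Inputs not in the document, assumed over a range:** f, the share of analysed participants who are in a same-arm family pair, and ICC, the within-pair correlation of the 12-month change given arm and ethnic group.

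**Step 1. Reproduce the plan's figures under independence.**

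- n per arm = 2 × [0.454 × (1.960 + 0.842) / 0.107]² = 282.6, so 283. The plan has 277, about 2% lower. A one-sided alpha would give 223 and does not fit.
- Standard error at 277 per arm = 0.454 × √(2/277) = 0.0386. The ratio 0.107/0.0386 is 2.774, and power = Φ(2.774 − 1.960) = 79.2%.
- Drop-out: 554/0.8 = 692.5, stated as 692.

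The plan's figures therefore correspond to fully independent participants (design effect 1.00). The starting point is 79.2%, slightly below 80% before any clustering is considered.

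**Step 2. Design effect for pairs.** In an arm of n people with a fraction f in pairs, there are nf/2 pairs, and each adds a covariance of 2 × ICC × SD² to the variance of the arm total. That variance is n × SD² × (1 + f × ICC), so

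DE = 1 + f × ICC.

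**Step 3. Consequences.**

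- The model standard error is too small by a factor of √DE.
- True two-sided type I error of the unadjusted test = 2 × [1 − Φ(1.960/√DE)].
- Power of a correctly adjusted test = Φ(2.774/√DE − 1.960).

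| f | ICC | DE | √DE | Type I error | Power | Loss from 79.2% |
|---|---|---|---|---|---|---|
| 0 | – | 1.00 | 1.000 | 5.0% | 79.2% | – |
| 10% | 0.1 | 1.01 | 1.005 | 5.1% | 78.8% | 0.4 points |
| 20% | 0.2 | 1.04 | 1.020 | 5.5% | 77.6% | 1.6 points |
| 30% | 0.3 | 1.09 | 1.044 | 6.0% | 75.7% | 3.5 points |

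For the second row, for example, 1.960/1.005 = 1.950, which gives 5.1%, and 2.774/1.005 − 1.960 = 0.800, which gives 78.8%.

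Family units larger than two would raise DE above 1 + f × ICC. A correlation of zero removes the problem, and a negative one would reverse its direction.

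**The case against.** The strongest reply is that the effect may be negligible. Nothing in the document suggests that many relatives will enrol. Invitations go to people selected from HELIUS on their own characteristics, and each relative must separately meet the age, literacy, risk-factor and smartphone criteria. At f = 10% and ICC = 0.1 the interval widens by about 0.5%. This stands, and it is why the point is not graded higher.

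A second reply concerns direction. A reader might infer that the analysis is certain to be anti-conservative. The document does not support that. The relevant correlation is in the change of the composite, given arm and ethnic group, and not in shared levels of weight or diet. A positive value is plausible: the same-arm rule itself presumes that relatives influence each other, and the intervention targets diet and exercise, which partners may share. It is not demonstrated, however. Shared coaching adds little to the argument, since coaches are matched by ethnic group, so unrelated participants share them too, and the control arm has none.

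Third, a reader might attribute the whole gap below 80% to clustering. That would be wrong: 0.8 points of it are already there with independent participants.

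Fourth, this is a condensed article and a full analysis plan may add a family term. That would settle the matter. But the article is not merely silent on clustering. It names a level, and that level does not match its own allocation rule. The freedom left by choosing intercept or slope on model fit concerns ethnic groups only. The baseline-imbalance and imputation sensitivity analyses do not address families either.

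**Conclusion.** The concern holds in conditional form. The allocation rule makes the family the unit of allocation for related participants, and neither the stated primary model nor the sample size reflects this. If within-family correlation of the 12-month change is positive, the primary standard error is too small and the power overstated.

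Over the assumed range of 10% to 30% of participants in pairs and ICC 0.1 to 0.3, the type I error is 5.1% to 6.0% and power 78.8% to 75.7%, against 79.2% under independence. Both inputs are assumptions, so these figures show scale and are not estimates for this trial. The effect is probably modest.

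A reader might go further and conclude that the primary analysis is unsound or that the trial must recruit more people. The document supports neither, because it gives no family share and no correlation. This is a should-fix item, to be settled before the analysis is locked.

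**What to change.** 1. **Keep a family-unit identifier** in the analysis data set, with unrelated participants as units of one. Applying the same-arm rule already requires these links to be known.
2. **Account for the family unit in the primary model and every model that copies it**, through family-clustered robust standard errors or a family random intercept. The ethnic-group term can remain, as it serves a different purpose.
3. **Report** the number of participants with a relative in the trial, by arm, and the sizes of the family units.
4. **Reword the power statement**: the 80% assumes independent participants, is about 79% at 277 per arm on the stated inputs, and is lower to the extent that related participants enrol. No additional recruitment is proposed.

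The cost is one variable and a sentence or two in the analysis plan. The primary interval may become slightly wider and the stated power slightly lower. If few relatives enrol, the results will barely change.
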